### Sample Size

The MYCHOICE study is a noninferiority trial for which we hypothesize that MR-HIFU is noninferior to the group of standard (minimally) invasive treatments, accepted by a ≤15 points difference in symptom reduction at 24 months’ follow-up as determined with the SSS (range 0-100 points) part of the UFS-QoL questionnaire. We expect that women participating in this trial have a slight preference for the noninvasive MR-HIFU treatment. We therefore choose to use an unbalanced design in which participants are allocated to the intervention or usual care group at a 2:1 ratio, resulting in a larger sample size in the MR-HIFU treatment group. With a larger sample size of the MR-HIFU treatment group, we will be able to gather more data on this new treatment while the effectiveness of standard care is already much better documented. Randomization, stratified by center, will be performed using a computer-generated randomization system, which randomly selects block sizes of 3, 6, or 9. Previous studies concerning (minimally) invasive treatments were performed with women with an average baseline UFS-QoL SSS of 55-65 points [33]. Treatment initiated a decrease of 30-47 points on SSS 12 months after these combined treatments. Hitherto, there are 2 MR-HIFU studies published that used a full ablation protocol, had the same 12-month follow-up period as the studies on (minimally) invasive treatments, and in which women participated with a baseline UFS-QoL SSS of 55-65 points. These women showed an SSS reduction of 30-40 points at follow-up [34,35]. In our study population we expect comparable baseline SSS in the MR-HIFU and standard care group. However, because hysterectomy results in a somewhat higher SSS reduction than the uterus-saving treatments, we assume in our power calculation an a priori 5-point delta between both the MR-HIFU and standard care group in favor of the standard care group. Using a noninferiority margin of 15 points with α (1-sided)=0.025, β=.1, and an SD of 20 points, we estimate that 192 participants (128 patients in the MR-HIFU treatment group and 64 patients in the [minimally] invasive treatment group) will be required to test noninferiority of MR-HIFU. Anticipating a 20% loss to follow-up, we need to include 160 patients in the MR-HIFU group and 80 patients in the (minimally) invasive treatment group. The noninferiority margin and the SD of 20 points were determined in consultation with the Dutch Society for Obstetrics and Gynecology and were similar to the noninferiority margin used in the MYOMEX-2 study [36].

### Recruitment

In all participating hospitals, patients will be recruited during a visit at the gynecologist. Furthermore, a study website is created to inform patients from all over the country, providing information and contact details to directly contact the study team. By promoting this website among general practitioners, gynecologists, and potential participants, we expect women with an interest in MR-HIFU to become acquainted with our study. Because MR-HIFU treatment for uterine fibroids is not reimbursed in the Netherlands, participating in the MYCHOICE study is the only possibility for women to undergo MR-HIFU treatment.

### Statistical Methods

In this study, data will initially be analyzed on an intention-to-treat-basis (including treatment failures) but a per-protocol analysis will also be performed. QoL at the follow-up time point of 24 months after treatment is determined as a change in SSS between baseline and 24 months’ follow-up. The difference between the symptom reduction after MR-HIFU and standard (minimally) invasive fibroid care including 97.5% CI is determined using linear regression analysis with a correction for baseline SSS. Although symptom reduction 24 months after MR-HIFU will be expected to be noninferior to standard (minimally) invasive fibroid care, the time course of symptom reduction may differ between the 2 treatment arms. This will be investigated with longitudinal covariance analysis. A faster symptom reduction in the usual care arm may be caused by a faster symptom reduction after hysterectomy. Therefore, a subgroup analysis in which the individual treatments are compared will be performed.

Patients can leave the study at any time for any reason if they wish to do so, without any consequences. In case they decide to withdraw before treatment or within the first 3-month follow-up, they will be included in the database, but an additional patient will be included to achieve the required sample size and reach primary outcome. In case patients withdraw after the 3-month follow-up, they are considered nonresponders. As much precautions as possible will be taken to prevent missing data. However, missing values are expected to occur in our trial due to technical failures and loss to follow-up. In case missing data reach 5%, additional analyzes will be performed to identify a plausible assumption, that is, missing not at random, missing at random, or missing completely at random. Subsequently, an analysis method that is valid under that assumption will be used.

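### The protocol plans both an ITT and a per-protocol analysis but does not require them to agree, so control women who decline treatment could help carry a noninferiority claim resting on ITT alone

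*Protocol article*

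**What the plan says.** The Sample Size section states that "The MYCHOICE study is a noninferiority trial", with the 24-month change in symptom severity score (SSS) as the measure. The design inputs are given as "Using a noninferiority margin of 15 points with α (1-sided)=0.025, β=.1, and an SD of 20 points", together with "an a priori 5-point delta between both the MR-HIFU and standard care group in favor of the standard care group". On analysis sets, the Statistical Methods section says that "data will initially be analyzed on an intention-to-treat-basis (including treatment failures) but a per-protocol analysis will also be performed". It gives the order of the two analyses but no rule for combining them, and it does not say who belongs to the per-protocol set.

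Two statements bear on adherence. Sample Size: "We expect that women participating in this trial have a slight preference for the noninvasive MR-HIFU treatment". Recruitment: "participating in the MYCHOICE study is the only possibility for women to undergo MR-HIFU treatment".

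Two others work in the opposite direction. Study Population and Eligibility requires that a woman be motivated, before entry, for one of the three control treatments. Statistical Methods provides that women who withdraw before treatment or within the first three months stay in the database and that an additional patient is included.

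**The concern.** In a superiority trial, untreated women kept in the ITT set usually make the result more cautious. In a noninferiority trial, untreated women in the control arm do the reverse. They lower the mean improvement on standard care, so MR-HIFU looks closer to it than it is to the treatments actually given.

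This is foreseeable here. Treatment is not blinded, some women will enter because they want MR-HIFU, and a woman allocated to standard care cannot obtain MR-HIFU elsewhere in the Netherlands. If she declines surgery or embolization and still returns questionnaires, she counts as a control with little or no improvement. The per-protocol analysis would show whether the conclusion depends on such women, but nothing stated makes the claim wait for it. The result is meant to support reimbursement and guideline inclusion, so a claim that control refusal could help produce is worth guarding against in advance.

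**Working it through.** **Inputs from the protocol (Sample Size).** Margin 15 points, one-sided alpha 0.025, power 90%, SD 20, assumed true difference 5 points in favour of standard care, 2:1 allocation ("participants are allocated to the intervention or usual care group at a 2:1 ratio"), 20% dropout ("Anticipating a 20% loss to follow-up"). Earlier studies of the control treatments showed SSS reductions of 30-47 points at 12 months.

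**Assumptions not in the documents.** The share f of analysed controls who are untreated (5% or 10%). Their improvement without treatment (0 or 10 points). No untreated women in the MR-HIFU arm. The 12-month reductions are carried over to 24 months.

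**Reproducing the sample size.** Controls = (1 + 1/2) × 20² × (1.960 + 1.282)² / (15 − 5)² = 63.04, rounded up to 64. With 128 on MR-HIFU the total is 192, and 64/0.8 + 128/0.8 = 80 + 160 = 240. Both totals match the protocol.

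**Standard error and reference values.** SE = 20 × √(1/128 + 1/64) = 3.062. Let D be the mean reduction on standard care minus that on MR-HIFU. Then P(declare noninferiority) = Φ((15 − D)/SE − 1.96). At D = 5 this is 90.4%; at D = 15 it is 2.5%.

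**Effect of untreated controls.** If a fraction f of controls forgo a benefit b, the ITT difference falls by f × b. With a true deficit of 15 among treated women, P = Φ(f × b/3.062 − 1.96). The value b = 20 is the mildest case (30 points if treated, 10 if not). The others assume no improvement without treatment. The last column widens the control SD for the mixture, √(400 + f(1 − f)b²).

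| f | b | Shift | ITT difference | P, SD 20 | P, widened SD |
|---|---|---|---|---|---|
| 5% | 20 | 1.0 | 14.0 | 5.1% | 5% |
| 5% | 30 | 1.5 | 13.5 | 7.1% | 7% |
| 5% | 40 | 2.0 | 13.0 | 9.6% | 9% |
| 5% | 47 | 2.35 | 12.65 | 11.7% | 11% |
| 10% | 20 | 2.0 | 13.0 | 9.6% | 9% |
| 10% | 30 | 3.0 | 12.0 | 16.4% | 15% |
| 10% | 40 | 4.0 | 11.0 | 25.7% | 22% |
| 10% | 47 | 4.7 | 10.3 | 33.5% | 26% |

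**Offset from the MR-HIFU arm.** Suppose 6 of 64 controls and 4 of 128 MR-HIFU women are untreated with no improvement, and treated gains are 30-47 on standard care and 15-32 on MR-HIFU (a true deficit of 15). The control shift is 6/64 × 30 to 6/64 × 47 = 2.8 to 4.4 points. The MR-HIFU offset is 4/128 × 15 to 4/128 × 32 = 0.5 to 1.0. The chance of declaring noninferiority is then about 12-20%, against about 15-30% without the offset. If only the MR-HIFU arm has untreated women (5%, each losing 35 points), a true difference of 5 becomes 5 + 1.75 = 6.75 and power drops to about 77%.

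**Per-protocol power.** Excluding 10% of controls leaves 57.6 on average. SE = 20 × √(1/128 + 1/57.6) = 3.17, and power at D = 5 is Φ(10/3.17 − 1.96) = 88.3%. With 20% or 30% excluded it is 85.6% or 82.1%.

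**The case against.** The strongest reply is that the protocol already plans both analyses, and that stating ITT first sets an order, not a decision rule. A reader might infer that the per-protocol result plays no part in the claim. The text does not say so. It is silent on how the two results combine, and a separate analysis plan or full protocol may settle it. This stands: the point is a safeguard to add, not an error in a stated rule.

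A reader might also infer that non-adherence will fall mainly on controls, so that ITT is inherently anti-conservative in this design. The documents do not support that either. Only a slight preference is expected, women must be motivated for a control treatment before entry, control women choose among three options with their gynecologist, and no passage predicts refusal. Untreated women in the MR-HIFU arm push the other way. The direction therefore depends on where refusal falls.

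The mechanism is narrower than it first appears. It needs women who decline treatment, stay in the study and contribute a primary outcome. Withdrawals before treatment or within three months lead to an additional inclusion, and those women may have no 24-month score. The time point is counted from treatment, so it is undefined for a woman never treated, and a woman who only postpones is measured 24 months after her eventual treatment. Symptom medication could also give untreated women some improvement.

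Finally, the 2.5% error rate holds for the effect of assignment, a reasonable target in a pragmatic trial. It is exceeded only with respect to the effect of the treatments received. The per-protocol analysis gives up the protection of randomization and has its own selection bias. All of this limits the size and certainty of the concern. It does not remove the case for requiring the two planned analyses to agree.

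**Conclusion.** The point holds in a limited form, as an inexpensive improvement. As written, the protocol permits a noninferiority claim on ITT alone, and control women who decline treatment but remain in follow-up would move that analysis toward noninferiority. At a true 15-point deficit the chance of a positive conclusion would be about 5-12% with 5% of controls untreated and about 10-34% with 10%, instead of 2.5%. These figures rest on an assumed refusal rate, an assumed forgone benefit of 20-47 points, SD 20, 128 versus 64 analysed, and full adherence in the MR-HIFU arm. Widening the control SD lowers the upper ends to about 11% and 26%, and some MR-HIFU non-adherence lowers them further. They illustrate sensitivity and do not predict the trial's error rate.

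**What to change.** Keep the ITT analysis and add one rule: noninferiority is concluded only if the confidence limit excludes a 15-point deficit in both the ITT and the per-protocol analysis. Define the per-protocol set as women who received a treatment belonging to their allocated arm. Women with a later reintervention stay in the set, so that MR-HIFU failures are not removed from it.

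The change takes a sentence or two, and the second analysis is already planned. It costs some power: about 88% in the per-protocol set instead of 90% if about 10% of controls are excluded, and the joint requirement cannot exceed that figure. Because the per-protocol comparison is open to selection bias, it should supplement ITT and not replace it. If an analysis plan already contains such a rule, a reference to it is enough.

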Other study parameters	Several patient characteristics are collected from the medical record of the patients and from the baseline questionnaire such as age, amount and size of fibroids, location of fibroid, position of uterus, duration of treatment, ethnicity, parity, height, weight, relevant medical, and medical history.	Data analysis will be stratified by center to check for differences in results between centers.	In case necessary, multilevel analysis will be used to correct for differences between centers. Multivariate analysis will be performed for symptom reduction, QoL improvement, and reintervention correcting for comedication or menopause as possible confounder. In addition, we will investigate whether certain baseline characteristics such as age, BMI, number of uterine fibroids, and target fibroid size are associated with symptom reduction and reintervention using linear, logistic, and Cox regression analysis.

^a^MYCHOICE: MYoma treatment Comparison study: High-intensity image–guided fOcused ultrasound versus standard (minimally) Invasive fibroid care—a (Cost-)Effectiveness analysis.

^b^QoL: quality of life.

^c^UFS-QoL: Uterine Fibroid Symptom and Quality of Life questionnaire.

^d^EQ-5D-5L: 5-level version of the EuroQoL questionnaire.

^e^SSS: symptom severity score.

^f^PREM: patient-reported experience measurement.

^g^MR-HIFU: magnetic resonance image–guided high-intensity focused ultrasound.

^h^NPV: nonperfused volume.

^i^MRI: magnetic resonance imaging.

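### Randomisation is stratified by centre, but the stated primary regression leaves centre out; the noninferiority test becomes slightly conservative, and the role of the later centre correction is unclear

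*Protocol article*

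**What the plan says.** Three places in the protocol article bear on this.

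- **Sample Size** gives the allocation scheme: "Randomization, stratified by center, will be performed using a computer-generated randomization system, which randomly selects block sizes of 3, 6, or 9". Allocation is 2:1.
- **Statistical Methods** gives the primary analysis. The difference between arms in SSS change from baseline to 24 months "is determined using linear regression analysis with a correction for baseline SSS". Baseline SSS is the only covariate named.
- **Secondary Outcomes, Table 2, row on other study parameters** is the only place where centre enters an analysis. It says "Data analysis will be stratified by center to check for differences in results between centers", and then "In case necessary, multilevel analysis will be used to correct for differences between centers".

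The article does not say what would make the correction necessary. Nor does it say whether the multilevel model would replace, supplement or stand apart from the regression in Statistical Methods.

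**The concern.** Blocking within centre keeps the arms close to 2:1 in every centre, so a difference between centres that affects both arms alike largely cancels out of the arm comparison. A regression without centre still counts that variation as residual noise. The reported standard error is then larger than the real sampling variation of the estimate, and the interval compared with the 15-point margin is wider than it should be. The trial stratifies by centre and then does not collect the precision that this buys.

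The second issue is clarity. The only route by which centre can enter is a correction triggered by an undefined condition after the results by centre have been inspected. In an open-label noninferiority trial, the reader should know beforehand which single model is held against the margin.

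**Working it through.** **Inputs from the Sample Size section.** "Using a noninferiority margin of 15 points with α (1-sided)=0.025, β=.1, and an SD of 20 points"; "we assume in our power calculation an a priori 5-point delta between both the MR-HIFU and standard care group", in favour of standard care; "participants are allocated to the intervention or usual care group at a 2:1 ratio"; 128 + 64 evaluable patients; 20% loss to follow-up.

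**Assumed inputs.** The article gives neither the number of centres nor the share of variance due to centre (ICC). I take ICC = 0.02, 0.05 and 0.10, and 6, 10 or 15 centres. The SD of 20 is treated as the residual SD of the primary model.

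**Step 1: reproduce the plan's figure.** The distance from the assumed difference to the margin is 15 − 5 = 10 points. Standard-care patients = (1.96 + 1.2816)² × 20² × (1 + 1/2) / 10² = 63.04, rounded up to 64. MR-HIFU patients = 2 × 64 = 128, total 192. Dividing by 0.8 gives 80 + 160 = 240. Both totals agree with the article. The formula has no centre term.

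**Step 2: standard error without centre.** SE = 20 × √(1/128 + 1/64) = 3.06. Power = Φ(10/3.06 − 1.96) = 90.4%.

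**Step 3: standard error with centre, effects shared by both arms.** SE = 3.062 × √(1 − ICC). Power with centre = Φ(10/SE − 1.96). If centre is left out, the estimate varies with this smaller SE but is judged with 3.062. Its power is therefore Φ((10 − 1.96 × 3.062)/SE) and its true one-sided error rate is 1 − Φ(1.96 × 3.062/SE).

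| ICC (assumed) | SE with centre | Power with centre | Power without centre | One-sided error rate without centre |
|---|---|---|---|---|
| 0 | 3.06 | 90.4% | 90.4% | 2.5% |
| 0.02 | 3.03 | 91.0% | 90.7% | 2.4% |
| 0.05 | 2.98 | 91.8% | 91.0% | 2.2% |
| 0.10 | 2.90 | 93.1% | 91.6% | 1.9% |

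Against the planned 90.4%, a model with centre gains about 0.5, 1.4 or 2.7 points. Compared with the model without centre under the same ICC, the gain is about 0.3, 0.8 or 1.5 points.

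**Step 4: simulation.** Centre-stratified 2:1 blocks of 3, 6 or 9, 192 patients, total SD 20, no baseline covariate. There were 6,000 runs for the error rate (Monte Carlo error √(0.025 × 0.975/6000) ≈ 0.002) and 4,000 for power. Ranges are over 6, 10 and 15 centres.

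| ICC | SE without / with centre | Error rate without / with | Power without / with |
|---|---|---|---|
| 0.02 | 3.05–3.06 / 3.03–3.05 | 0.022–0.024 / 0.023–0.025 | 0.90–0.91 / 0.90–0.92 |
| 0.05 | 3.04–3.05 / 2.98–3.00 | 0.024–0.026 / 0.024–0.027 | 0.90–0.91 / 0.91–0.92 |
| 0.10 | 3.02–3.05 / 2.90–2.92 | 0.017–0.023 / 0.023–0.028 | 0.91–0.92 / 0.93 |

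The standard errors agree with the formula. The shortfall in the error rate is within simulation noise at ICC 0.05 and becomes visible only at about 0.10.

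**The case against.** **The article is condensed, and the handling of centre may be left to an analysis plan.** This stands in part. Random versus fixed effects, the pooling rule for small centres, and centre terms in the longitudinal, patient-experience and Cox models can all be left there. But the article is not silent on the primary model: it names the covariate set, omits the stratification factor and attaches an undefined condition to centre.

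**The error is in the safe direction.** This stands. The interval is too wide rather than too narrow, and the planned 90% power takes no credit for centre.

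**Centre effects may not be shared by both arms.** This stands as a limit on the benefit. MR-HIFU is given at only two hospitals, while control patients can be treated in their own (Study Design and Setting; Pretreatment). In a simulation with the centre effect on controls only, at ICC 0.05, a centre intercept gained nothing (SE 3.05 without, 3.07 with) and the error rate was the same in both models. That would be treatment-by-centre heterogeneity, which a centre intercept does not address.

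**A reader might infer two competing primary results, with the choice made after seeing the data.** The article does not support that. The conditional sentence sits in the table of secondary outcomes and is not expressly tied to the regression in Statistical Methods. The same cell does go on to mention symptom reduction, so its reach is unclear, but unclear is all that can be said. Even if noninferiority were claimed when either model passed, simulation with shared effects put the error rate at about 2.4–2.9%, with the two models disagreeing in 0.2–0.8% of trials at the margin.

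**Conclusion.** The point holds in a limited form. The stated primary regression does not include the factor by which the trial randomises, and the only provision for centre is conditional, undefined and of unclear relation to the primary model.

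The numerical effect is small and depends on an assumed ICC. With 2–10% of variance due to centre and effects common to both arms, the standard error is overstated by about 1–5% (3.06 against 3.03–2.90). About 1 to 3 points of power above the planned figure are not collected, or up to 1.5 points when the two models are compared under the same ICC. At ICC 0 nothing changes. If centre effects act in one arm only, little or nothing is gained.

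A reader might take the wrongly sized standard error as a threat to the noninferiority conclusion. It is not: leaving out a shared centre effect makes the test mildly conservative, so it does not raise the risk of a false claim. The sample size needs no change.

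**What to change.** State the primary model as: SSS change at 24 months = arm + baseline SSS + randomising centre. Centre is the hospital in whose stratum the patient was randomised, not the hospital that gave MR-HIFU. Enter it as a random intercept, or as fixed effects with very small centres pooled by a rule written down beforehand. Remove the conditional wording in Table 2 as far as the primary outcome is concerned, and say that the results by centre are descriptive only and do not alter the primary model.

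The cost is a change of wording before data lock and a few degrees of freedom. No extra patients or data are needed, and 192 evaluable and 240 randomised remain as planned.

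### The primary noninferiority interval rests by default on one common variance, in a 2:1 trial with a mixed smaller arm; the departure from 2.5% is modest, and a robust standard error removes most of it (minor)

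*Protocol article*

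**What the plan says.** The Statistical Methods section fixes the primary analysis. The outcome is the change in SSS from baseline to 24 months, and the between-arm difference with a 97.5% CI "is determined using linear regression analysis with a correction for baseline SSS". It does not name the variance estimator or say whether the interval is one- or two-sided.

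The Sample Size section sets the design: "participants are allocated to the intervention or usual care group at a 2:1 ratio". Its planning values are: "Using a noninferiority margin of 15 points with α (1-sided)=0.025, β=.1, and an SD of 20 points". It assumes "an a priori 5-point delta between both the MR-HIFU and standard care group in favor of the standard care group", and gives as the reason: "because hysterectomy results in a somewhat higher SSS reduction than the uterus-saving treatments". It cites SSS decreases of 30-47 points at 12 months after the standard treatments and 30-40 points after MR-HIFU.

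Under Control Group, women allocated to standard care choose between hysterectomy, myomectomy and UAE together with their gynecologist. The Strengths section expects hysterectomy to have a limited influence on the control-arm result, because most participants should prefer to keep the uterus. It gives no expected percentage.

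**The concern.** Ordinary regression estimates one residual variance from all patients and applies it to both arms. With equal arms this does no harm to the standard error of the difference. At 2:1 the larger arm dominates the pooled variance, while the smaller arm contributes most of the true sampling variance. If the smaller arm is the more variable one, the standard error is too small and the test is too liberal. If it is the less variable one, the test is too strict.

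Here the smaller arm combines treatments that the protocol itself expects to differ in effect, and this adds between-treatment variance to that arm. In a noninferiority trial, a standard error that is too small makes it easier to claim noninferiority wrongly. The result is intended to support reimbursement and guideline inclusion, so the level of this one test matters.

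**Working it through.** **1. The plan's own figure.** Inputs from Sample Size: margin 15, assumed difference 5, SD 20, one-sided α 0.025, power 90%, ratio 2:1.

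Control n = (1 + 1/2) × [20 × (1.960 + 1.282) / (15 − 5)]² = 63.04, rounded up to 64. MR-HIFU n = 128, total 192. Dividing by 0.8 for 20% loss gives 80 + 160 = 240. The stated numbers reproduce, and power at 128/64 is 90.4%.

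**2. Formula for the actual error.** With arm SDs s_T (MR-HIFU) and s_C (control):

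- Pooled variance V = (127 s_T² + 63 s_C²) / 190
- Standard error used = √[V × (1/128 + 1/64)]
- True standard error = √(s_T²/128 + s_C²/64)
- One-sided error at the margin = 1 − Φ(1.96 × standard error used / true standard error)

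This is a large-sample formula that takes the SDs as residual SDs. Step 5 checks it in the baseline-adjusted regression.

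**3. The case built from the protocol's figures.** Take the ends of the cited range, 30 and 47 points, mixed half and half, with SD 20 within each treatment. The between-treatment SD is 17 × √(0.5 × 0.5) = 8.5, so s_C = √(400 + 72.25) = 21.73. With s_T = 20:

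- V = 423.96; standard error used = 3.152; true standard error = 3.241; ratio = 0.973
- Error = 1 − Φ(1.96 × 0.973) = 1 − Φ(1.906) = 2.8%

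With only 20% of the arm at 47 and the rest at 30, s_C = √(400 + 17² × 0.2 × 0.8) = 21.12 and the error is 2.7%.

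**4. Assumed SDs, to show the range.** None of the unequal pairs is in the protocol.

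| MR-HIFU SD / control SD | Standard error used | True standard error | One-sided error |
|---|---|---|---|
| 20 / 20 | 3.062 | 3.062 | 2.5% |
| 20 / 25 | 3.335 | 3.590 | 3.4% |
| 20 / 15 | 2.831 | 2.577 | 1.6% |

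With 96 per arm, the error is 2.5% in every row. The effect therefore needs both the 2:1 ratio and unequal variances.

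**5. Simulation of the baseline-adjusted regression** (30,000 trials per scenario, true difference at the margin).

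| Scenario | Ordinary standard error | HC2 standard error |
|---|---|---|
| Equal SDs, 20/20 | 2.5% | 2.4% |
| Control half 30, half 47 points, SD 20 within | 2.8% | 2.5% |
| 20/25 | 3.5% | 2.7% |
| 20/15 | 1.6% | 2.4% |

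The Monte Carlo standard error near 2.5% is √(0.025 × 0.975 / 30,000) = 0.09 percentage points. The ordinary results agree with the formula, and HC2 brings each scenario close to the nominal level.

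**6. Sidedness.** The figures above use 1.96, which matches "α (1-sided)=0.025". If the 97.5% CI were two-sided, the nominal one-sided level would be 1.25%. The ordinary interval would then give 1.46% for the half-and-half mix and 1.87% for 20/25. Power at 128/64 would fall from 90.4% to 84.7%.

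**The case against.** The strongest objection is that the article never says the variance is pooled. It names linear regression only, and the type of standard error is commonly left to a full protocol or SAP, which is not shown. This stands in part. Pooling is the ordinary meaning of the method named, but an unseen SAP may already specify robust errors, and then nothing needs to change.

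The second objection is size. The only SD in the protocol is 20 for both arms. If that value already describes the mixed control arm, the error is exactly 2.5%. The half-and-half mix is also a strong reading. The protocol reports 30-47 points for the standard treatments together, does not assign the ends to particular treatments, calls the hysterectomy advantage modest, and expects its influence to be limited. All of this stands, and it keeps the point minor.

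A reader might infer that the mixed arm can push the error either way. It cannot. Mixing treatments of different mean effect only adds variance to the smaller arm, so it only raises the error. A value below 2.5% needs a smaller spread within the control treatments, for example many scores near zero after hysterectomy, and the protocol gives no figure for that. A reader might also extend the point to the longitudinal analysis. The article does not describe that model's covariance structure, so no defect can be shown there.

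**Conclusion.** The point holds as a minor one. The design facts are in the text, and the mechanism is confirmed by formula and by simulation. On the protocol's figures, the one-sided error would be about 2.7-2.8% at a nominal 2.5%. This assumes a model-based standard error, a within-treatment SD of 20 in both arms, effects at the ends of the cited range, and a one-sided 97.5% limit.

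It would be tempting to conclude that the trial does not control its type I error. The documents do not support that. The values of 3.4% and 1.6% rest on SDs assumed for illustration. If the interval were two-sided, the error in the half-and-half and 20/25 cases would stay below 2.5%. The stated sample size is arithmetically correct and is not affected while both SDs are 20.

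**What to change.** Keep the linear regression, the baseline SSS covariate and the sample size. Before outcome data are examined, specify that the primary confidence limit uses HC2 or HC3 standard errors, or a separate residual variance per arm. In the same sentence, state that the 97.5% interval is one-sided, so that the limit is tested at one-sided 0.025 as in the sample size calculation.

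The cost is a line or two in the analysis plan. With HC2 or HC3 the point estimate does not change. If the variances are in fact equal, the test becomes very slightly conservative (about 2.3-2.4% instead of 2.5%). If the SAP already says this, no action is needed.
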